## Abstract

**Introduction:**

Many surgical techniques have been used to repair abdominal wall defects in the inguinal region based on the anatomic characteristics of this region and can be categorised as ‘tension’ repair or ‘tension-free’ repair. Tension-free repair is the preferred technique for inguinal hernia repair. Tension-free repair of inguinal hernia can be performed through either the anterior transversalis fascia approach or the preperitoneal space approach. There are few large sample, randomised controlled trials investigating the curative effects of the anterior transversalis fascia approach versus the preperitoneal space approach for inguinal hernia repair in patients in northern China.

**Methods and analysis:**

This will be a prospective, large sample, multicentre, randomised, controlled trial. Registration date is 1 December 2016. Actual study start date is 6 February 2017. Estimated study completion date is June 2020. A cohort of over 720 patients with inguinal hernias will be recruited from nine institutions in Liaoning Province, China. Patient randomisation will be stratified by centre to undergo inguinal hernia repair via the anterior transversalis fascia approach or the preperitoneal approach. Primary and secondary outcome assessments will be performed at baseline (prior to surgery), predischarge and at postoperative 1 week, 1 month, 3 months, 1 year and 2 years. The primary outcome is the incidence of postoperative chronic inguinal pain. The secondary outcome is postoperative complications (including rates of wound infection, haematoma, seroma and hernia recurrence).

**Ethics and dissemination:**

This trial will be conducted in accordance with the Declaration of Helsinki and supervised by the institutional review board of the Fourth Affiliated Hospital of China Medical University (approval number 2015–027). All patients will receive information about the trial in verbal and written forms and will give informed consent before enrolment. The results will be published in peer-reviewed journals or disseminated through conference presentations.

**Trial registration number:**

NCT02984917; preresults.

Strengths and limitations of this studyThis trial will be the first prospective multicentre randomised controlled study involving nine institutions in Liaoning province of Northern China to provide reliable results from a representative study population.This trial will compare postoperative complications after anterior transversalis fascia approach versus preperitoneal space approach for inguinal hernia repair in residents in Northern China.Based on ethical and economic considerations, interim analysis will be performed during the trial to reduce unnecessary waste of manpower and materials (lower cost).The limited time for studying postoperative recurrence of hernia likely influences the judgement of long-term recurrence of inguinal hernia.Variability of surgeons from each study centre could be a major confounder to bias the results of this trial.

## Background

### History and current related studies

Inguinal hernia is a common surgical disease that manifests as protrusion of abdominal cavity contents through the inguinal canal because of an abdominal wall defect. It is more common in men than in women, with an overall incidence of 5%–10%.^1^ Methods for surgical repair of abdominal wall defects in the inguinal region are classified as either ‘tension’ repairs or ‘tension-free’ repairs. Herniorrhaphy through repair of the posterior wall of the inguinal canal was first described by Bassini in 1887 and is regarded as a classic surgical method.^2^

As understanding of the anatomic location and pathophysical characteristics of inguinal hernia developed, the American surgeon Lichtenstein proposed a new concept of tension-free herniorrhaphy.^3^ This technique was quickly adopted worldwide because of its advantages including minimal invasion, technical ease, effectiveness, low complication rate, low recurrence rate and allowance of resumption of unrestricted physical activity. The most common technique is open tension-free herniorrhaphy.

Tension-free herniorrhaphy methods include anterior transversalis fascia repair, preperitoneal repair, abdominal cavity patch repair and combined repair approaches.^4–6^ Lichtenstein herniorrhaphy is the representative technique of anterior transversalis fascia repair. Preperitoneal repair techniques include transabdominal preperitoneal, total extraperitoneal and Kugel repair techniques. The combined repair approaches refer to tension-free herniorrhaphy using a modified Kugel patch and the Ultrapro hernia system.^7 8^

Many surgical repair methods involving patches (of varying types and materials) are available for inguinal hernia repair. Zhu *et al*
9 performed a meta-analysis regarding open extraperitoneal approach and extraperitoneal laparoscopic hernioplasty for inguinal hernia repair. They found that these two approaches exhibited basically similar clinical outcomes. Patients receiving extraperitoneal laparoscopic hernioplasty needed shorter hospital stays and exhibited lower incidence of postoperative complications. Patients receiving open extraperitoneal approach exhibited lower incidence of peritoneal tears. Pisanu *et al*
10analysed the clinical efficacy of laparoscopic and Lichtenstein techniques in recurrent inguinal hernia repair. They found that laparoscopicy showed lower incidence of chronic inguinal pain and an earlier return to normal daily activities but greatly longer operative time. There are many randomised controlled trials^11–15^ on the clinical efficacy of inguinal hernia repair approaches (table 1), but little is reported on anterior transversalis fascia approach and preperitoneal space approach for inguinal hernia repair in residents in Northern China.

**Table 1 T1:** RCTs regarding inguinal hernia repair approaches

Study	Design	Subjects	Disease	Follow-up time	Outcome measures	Conclusion
Akhtar *et al*.^11^	RCT	TAPP (n=30) Lichtenstein (n=50)	Unilateral inguinal hernia	6 months	Average operation, pain score, analgesics, admission days, days required to return to work	Laparoscopic hernia surgery is better than Lichtenstein repair in terms of postoperative pain, hospital stay and return to daily activity.
Sarhan *et al*.^12^	RCT	A total of 200 patients scheduled for unilateral inguinal hernia repair were randomly divided into two groups to undergo either laparoscopic TAPP (group A) or open modified Kugel procedure	Unilateral inguinal hernia	32 months	Recurrence and short-term and long-term complications	Both open modified Kugel and laparoscopic TAPP preperitoneal repair techniques for inguinal hernia are safe and effective with low recurrence rates. Laparoscopic approach has better outcome in terms of chronic pain, short operative time and short duration of hospital stays.
Kargar *et al*.^13^	RCT	TAPP (n=60) Lichtenstein (n=60)	Inguinal herniajrnlTblFoot	Follow-up occurred within 6 weeks.	Pain score (VAS), haematoma/seroma, urinary retention, wound infection, hospital stay	The laparoscopic TAPP repair is safer and less complicated approach for inguinal hernia repair. The two main short-term advantages of the laparoscopic TAPP repair with the tension free Lichtenstein repair were less postoperative pain and earlier return to the normal life activities. No difference was seen in overall complications.
Salma *et al*.^14^	RCT	TAPP (n=30) Lichtenstein (n=30)	Direct inguinal hernia	Postoperative pain intensity assessed by VAS and hospital stay measured in hours.	Hospital stay, immediate post operative pain	There is less postoperative pain after laparoscopic repair but hospital stay is same in both the procedures but laparoscopic procedure does increase the cost.
Bahram^15^	RCT	TAPP (n=150) Lichtenstein (n=150)	Inguinal herniajrnlTblFoot	Three hundred patients with inguinal hernia were enrolled in this study, divided into two equal groups: Group I managed by TAPP laparoscopic repair and group II managed by open lichtenstein repair.	Operative time, intraoperative visceral injury, ileus, hospital stay or wound complications, postoperative pain, groin hypothaesia, return to activities, recurrence	TAPP technique is an excellent approach for treatment of inguinal hernia in comparison to LR either unilateral or bilateral, primary or recurrent inguinal hernia with low morbidity and recurrence comparable to that oflichtenstein repair with advantages of less postoperative pain and early return to activities.

LR, laparoscopic repair; RCT, randomised controlled trial; TAPP, transabdominal preperitoneal; VAS, Visual Analogue Scale.

There are few reports on the effects of different inguinal hernia repair approaches on postoperative complications, particularly regarding severe postoperative complications, in patients in northern China. The incidence of severe complications after inguinal hernia repair is relatively low, but this surgery can lead to physical impairment or organ dysfunction that greatly decreases patient quality of life and places a heavy burden on the patient’s family and society. At present, there is a scarcity of clinical evidence from large sample, randomised controlled trials investigating the effectiveness of inguinal hernia repair via the anterior transversalis fascia approach versus the preperitoneal approach.

### Main objectives

In this study, we will investigate the advantages and disadvantages of the anterior transversalis fascia approach versus the preperitoneal approach for inguinal hernia repair in residents from northern China regarding common postoperative complications (including acute and chronic pain, wound infection, rates of wound infection, haematoma, seroma and hernia recurrence) and severe postoperative complications. These outcomes will provide trial-based evidence for selection of rational therapeutic regimen in the clinic.

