**Figure 1 F1:**
[figure not shown]
Flow chart of study protocol. VAS, Visual Analogue Scale; SF-36, 36-Item Short Form Health Survey.

Predischarge, and 1 week, 1 and 3 months, 1 and 2 years after surgery: pain, wound infection, haematoma and seroma in the inguinal region and hernia recurrence will be recorded. Medical costs during hospitalisation and patient quality of life after discharge will be also recorded. The flow chart of study protocol is shown in figure 1. And The Standard Protocol Items: Recommendations for Interventional trials (SPIRIT checklist (Standard Protocol Items: Recommendations for Interventional Trials)) was followed in designing the study protocol (see online supplementary file 2).

10.1136/bmjopen-2017-016481.supp2Supplementary file 2

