### Study flowchart

#### Before surgery

Visit 1 (at admission, day 0)Sign informed consent;Recheck inclusion/exclusion criteria;Demographic data (sex, age, body height, body mass index) and medical insurance type;Type of hernia (indirect or direct);Inguinal hernia classification as type I, II, III or IV according to the adult inguinal hernia and femoral hernia classification (revised in 2003) developed by the Hernia and Abdominal Wall Surgery Group, Society of Surgery, Chinese Medical Association^19^;ASA classification;History of diseases and risk factors* (diabetes mellitus, cardiovascular disease, lung disease, peripheral vascular disease, dementia, hypertension, smoking history and alcohol use history) (*optional evaluation items);Disease onset and admission (interval from first appearance of the lump, main symptoms);Imaging examination (ultrasound, CT);Laboratory examination (routine blood testing, coagulation testing, testing of blood glucose, lipids and electrolytes and hepatic and renal function);Vital signs (body temperature, pulse, respiration rate, blood pressure);VAS pain score;Electrocardiography;Concomitant treatment.

The baseline information of patients with inguinal hernia included in this study is shown in table 2.

**Table 2 T2:** Baseline information of patients with inguinal hernia

Sex	Smoking history
Age	History of alcohol use
Body height	Disease attack and admission
Body mass index	Laboratory examination
Medical insurance type	Imaging examination
Type of hernia	Vital sign
Inguinal hernia classification	VAS pain score
Treatment time	ECG
American Society of Anesthesiologist Classification	Concomitant therapy
History of diseases	
Diabetes mellitus	
Cardiovascular disease	
Lung disease	
Peripheral vascular disease	
Dementia	
Hypertension	

VAS, Visual Analogue Scale.

Predischarge

Visit 2Vital signs (body temperature, pulse, respiration rate, blood pressure);Laboratory examination (routine blood testing, coagulation testing, testing of blood glucose, lipids and electrolytes and hepatic and renal function);Treatment regimen (inguinal hernia-specific treatment).

Surgical approach and patches (type and fixation method); anaesthesia method; drug name (generic preferred), dosage, route, start date, length of drug use will be recorded.Medical costs;Concomitant treatment.

Inguinal hernia-specific treatment, maintenance therapy and drugs used for concomitant treatment.Medical costs because of adverse events (AE).

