### Follow-up

Visit 3 (1 week after surgery via clinic visit or telephone follow-up)36-Item Short Form Health Survey (SF-36) score;Medical costs;Hernia recurrence (date and severity of recurrence). Recurrence will be diagnosed by the medical institutions, after being alerted by patients that symptoms are present.Presence or absence of haematoma and/or seroma;Wound infection (date and severity of wound infection).

Visit 4 (1 month after surgery via clinic visit or telephone follow-up)SF-36 score;Medical costs;Hernia recurrence (date and severity of recurrence). Recurrence will be diagnosed by the medical institutions, after being alerted by patients that symptoms are present.Presence or absence of haematoma and/or seroma;Wound infection (date and severity of wound infection).

Visit 5 (3 months after surgery via clinic visit or telephone follow-up)SF-36 score;Medical costs;Hernia recurrence (date and severity of recurrence). Recurrence will be diagnosed by the medical institutions, after being alerted by patients that symptoms are present.Presence or absence of haematoma and/or seroma;Wound infection (date and severity of wound infection).

Visit 6 (1 year after surgery via telephone follow-up)VAS pain score;SF-36 score;Medical costs;Hernia recurrence (date and severity of recurrence). Recurrence will be diagnosed by the medical institutions, after being alerted by patients that symptoms are present;Presence or absence of haematoma and/or seroma;Wound infection (date and severity of wound infection).

Visit 7 (2 years after surgery via telephone follow-up)VAS pain score;SF-36 score;Medical costs;Hernia recurrence (date and severity of recurrence). Recurrence will be diagnosed by the medical institutions, after being alerted by patients that symptoms are present;Presence or absence of haematoma and/or seroma;Wound infection (date and severity of wound infection).

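### Acute pain is a stated objective and early pain recording is promised, but the visit lists and Table 3 schedule no postoperative pain score before 1 year

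*Protocol article*

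**What the plan says.** Main objectives: the approaches are to be compared "regarding common postoperative complications (including acute and chronic pain, wound infection" and other complications. Acute pain is thus named alongside chronic pain.

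Study design, text below Figure 1: "Predischarge, and 1 week, 1 and 3 months, 1 and 2 years after surgery: pain, wound infection, haematoma and seroma in the inguinal region" are to be recorded. No instrument is named for pain.

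Abstract, Methods and analysis: "Primary and secondary outcome assessments will be performed at baseline (prior to surgery), predischarge and at postoperative 1 week, 1 month, 3 months, 1 year". The sentence closes with the 2-year assessment.

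Study flowchart, predischarge contact: the list opens "Visit 2Vital signs (body temperature, pulse, respiration rate, blood pressure);Laboratory examination" and continues with treatment regimen, costs and concomitant treatment. It has no pain item.

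Follow-up, 1 week: "Visit 3 (1 week after surgery via clinic visit or telephone follow-up)36-Item Short Form Health Survey (SF-36) score;Medical costs;Hernia recurrence", then haematoma or seroma and wound infection. The 1-month list, "Visit 4 (1 month after surgery via clinic visit or telephone follow-up)SF-36 score;Medical costs;Hernia recurrence", and the 3-month list have the same content. The VAS first appears after surgery in the 1-year list, and again at 2 years.

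Table 3: the VAS row is marked only at Visits 6 and 7. The adverse-event row runs from Visit 2 to Visit 7 and names wound infection, haematoma, seroma and recurrence, but not pain.

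Outcome measures: the primary outcome is chronic pain at 1 and 2 years. The secondary outcomes are a list of complications without acute pain. The other outcomes are SF-36 and cost utility.

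**The concern.** An objective needs a measurement, a time and a place among the outcomes. For acute pain, the objective and the design text point one way, while the lists and table that sites would work from point the other way. If the lists are followed, pain that arises and settles in the first weeks has no dedicated score, and a telephone call at 1 year cannot reconstruct it. A later analysis plan could not repair this, because it cannot analyse scores that were not taken.

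The Trial status section says recruitment is ongoing, so each patient who passes the early contacts without a score is a permanent loss for this objective. Early pain also features in the article's own background: four of the five trials in Table 1 list a pain score or postoperative pain as an outcome. That is context for why the objective matters, not evidence of an error.

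**Working it through.** No sample-size arithmetic applies. The article gives no figure for acute pain, and its calculation (10% against 3.4%, 600 evaluable patients) concerns chronic pain only. The check is a comparison of schedules, using the visit numbering of the Study flowchart and Follow-up sections.

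| Contact | Pain recording per Study design text | VAS in visit list | VAS mark in Table 3 | SF-36 (list and Table 3) |
|---|---|---|---|---|
| Before surgery | yes (preoperative VAS) | yes | no | no |
| Predischarge | yes | no | no | no |
| 1 week | yes | no | no | yes |
| 1 month | yes | no | no | yes |
| 3 months | yes | no | no | yes |
| 1 year | yes | yes | yes | yes |
| Last visit | yes | yes | yes | yes |

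Counts for the postoperative contacts before 1 year:

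- Contacts at which the design text promises pain recording: 4.
- Contacts with a VAS in the visit lists: 0 of 4.
- Contacts with a VAS mark in Table 3: 0 of 4.
- Contacts with an SF-36, which contains a bodily pain scale: 3 of 4.
- Contacts with no listed pain instrument of any kind: 4 − 3 = 1, the predischarge contact.

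Three further observations:

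1. The placing of the two VAS marks in Table 3 is unlikely to be an artefact of text extraction, because the visit lists independently give the same postoperative timing.
2. The design text promises pain, wound infection, haematoma, seroma and recurrence at every postoperative contact. The adverse-event row of Table 3 carries that list from Visit 2 onwards with one item missing: pain.
3. The abstract supports early assessment only indirectly. It says primary and secondary outcomes are assessed at all these times, but the primary outcome it names is chronic pain, and acute pain is in neither group.

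**The case against.** The strongest reply is that silence in the lists proves little, because they leave out other planned items. The predischarge list omits wound infection, haematoma, seroma and recurrence, although Table 3 marks them at that visit. Table 3 has no baseline VAS mark, although the text collects a preoperative VAS. Table 3 marks vital signs once, although the predischarge list has them too. Figure 1 is not shown, and its legend defines both VAS and SF-36. The full protocol and the eCRF are not shown either. The design text says pain will be recorded early, without tying it to the VAS.

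Much of this stands. A reader might infer that the trial cannot compare acute pain, that it has no measurement of it, or that the data will be missing for all 720 patients. The documents do not support that: they promise early pain recording in one place and omit the score in another.

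The objection does not remove the conflict. In each of the three examples, what one operational list omits the other supplies. For the early VAS, neither the visit lists nor Table 3 supplies it.

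The SF-36 is a partial answer. The article describes eight scale scores with a total in addition, so the bodily pain scale is not lost. But it is not groin-specific and starts only at 1 week, and the Statistical analysis section names just the SF-36 score for comparison.

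It is also fair to say that acute pain is one item in a bracketed list, and that the primary outcome and sample size do not depend on it.

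**Conclusion.** The point holds as an internal contradiction. The objectives and design text call for early pain data. The visit lists and Table 3 schedule a postoperative pain score at 0 of 4 contacts before 1 year, and acute pain has no named instrument or place among the outcomes. The consequence, no dedicated groin pain score in the acute period, follows if sites work from the lists and Table 3. Whether the eCRF or Figure 1 closes the gap cannot be seen, so a complete absence of early pain data is not established.

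This should be fixed, because the data cannot be recovered later and the remedy is cheap. It does not threaten the primary comparison and does not rank with faults that do.

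**What to change.** Add the VAS pain score for the operated groin to the predischarge, 1-week, 1-month and 3-month contacts in the Study flowchart and Follow-up lists and in the VAS row of Table 3, so that they match the Study design text. List acute pain as a secondary outcome compared between arms, and state which of these contacts count as acute.

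The cost is one short eCRF item at four contacts that already take place, plus an amendment. The instrument is already in the trial, and the 1- and 2-year visits already plan it by telephone, so the early telephone contacts need no new method.

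Patients already past these visits will lack the score. The acute-pain comparison should therefore be restricted by date of randomisation relative to the amendment, not by whether a score happens to exist. Patients randomised after that date remain a randomised comparison within centre, on a smaller number.

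If early pain scores will not be collected, remove acute pain from the Main objectives and early pain from the Study design text, and align the abstract's assessment times. This costs nothing in data collection but gives up a stated objective.

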### Distinguishing features from related studies

(1)This study will use centre-based stratification to investigate the effects of anterior transversalis fascia approach versus preperitoneal space approach for inguinal hernia repair on postoperative chronic inguigal pain and other common complications. This study will determine the optimal surgical hernia repair approach that is suitable for the anatomic characteristics of the inguinal region of residents in northern China and corresponds to the regional economic conditions. (2) Cost-utility analysis will be analysed using centre-based stratification. (3) To analyse the effects of different surgical repair approaches (involving various patch types and materials) on postoperative quality of life.

### Methods/Design

#### Study design

This is a prospective, large-sample, multicentre, randomised controlled trial that will include a cohort of over 720 patients with inguinal hernia. The trial committee organisation and contributions and role are provided in the see online supplementary file 1. In strict accordance with the Consolidated Standards of Reporting Trials standards,^16^ the baseline data (preoperative data), therapeutic regimen, therapeutic outcome and medical costs during hospitalisation of patients with inguinal hernia will be recorded. Patient data will be collected using an electronic data capture system (EDC).

10.1136/bmjopen-2017-016481.supp1Supplementary file 1

According to recommendations for treatment and follow-up of inguinal hernia repair in adults in the Guidelines for the Diagnosis and Treatment of Inguinal Hernia in Adults (2014 Edition) formulated by Chinese scholars^17^ and the Adult Inguinal Hernia Treatment Guidelines (Updated Edition in 2014) developed by the European Hernia Society,^18^ patients who undergo herniorrhaphy will be followed up at seven time-points: at baseline (at admission, visit 1), predischarge and at 1 week (visit 2), 1 month (visit 3), 3 months (visit 4, clinic visit or telephone follow-up), 1 year (visit 5, telephone follow-up) and 2 years after surgery (visit 6, telephone follow-up). The flow chart of the study protocol is shown in figure 1. Prior to surgery: patients will be rescreened against inclusion and exclusion criteria. Signed informed consent will be obtained. Patient’s demographic data, history of disease and medication and admission condition and vital signs will be recorded. Clinical examination data will be collected from each centre, including history of disease, physical examination, laboratory testing results, imaging findings, preoperative VAS pain score, intraoperative findings and details of occurrence and management methods of intraoperative injury to the intestinal tract and bladder, spermatic cord and vascular system.

